**Table 3. Adapted Healthier Families Intervention Modules and Key Messages**

| Session Number & Theme                | Key Messages                                                                                                                             |
|--------------------------------------------------|-------------------------------------------------------------------------------------------------------------------------------------------------|
| 1. Plan for Success                              | 1. Getting to Know You
2. How to turn “I want” into “I will”
3. Connect to Community Resources                                            |
| 2. Choose Healthy Foods                          | 1. Make Healthy Choices
2. Eat More Fiber and Less Sugar
3. Eat 5 Servings of Fruits and Veggies a Day                                    |
| 3. Be an Active Family Together                  | 1. Be Active Together
2. Keep Track of What You Do
3. Make it Fun                                                                         |
| 4. Plan Healthy Meals                            | 1. Plan Your Meals in Advance
2. Find Healthy Foods in the Store
3. Get the Most Bang for Your Buck
4. Reduce Food Waste               |
| 5. Healthy Snacks and Drinks                     | 1. Smart Snacking
2. Re-Think Your Drinks
3. Be Sugar Smart                                                                               |
| 6. Learning How to Unplug from Media and Screens | 1. Family Time Without Screens
2. Family Activities and Games                                                                                |
| 7. Mindful Eating                                | 1. Knowing When to Eat
2. Take Your Time: How to Slow Down and Enjoy Your Food
3. Plan Ahead for Meal and Snack Times                     |
| 8. Engaged Parenting                             | 1. Be an Engaged Parent in a Distracted World
2. Be the Mirror – How to Be a Healthy Role Model
3. Managing Anxiety for Parents and Kids  |
| 9. Eat Together                                  | 1. Healthy Plate, Healthy Family
2. Eat Together as a Family
3. Eat a Rainbow of Fruits and Vegetables                                    |
| 10. Find a Fitness Home                          | 1. Bringing Fitness to Your Home
2. Using Your Home Inside and Out
3. Using Parks and Greenspaces for Family Activity, While Staying Safe |
| 11. Sleep Matters                                | 1. Sleep Matters: Learn Why it is Important for You and Your Child
2. Know How Much Your Child Should Sleep
3. Plan Ahead and Keep Track  |

|                                                      |                                                                              |
|------------------------------------------------------|------------------------------------------------------------------------------|
| 12. Maintaining and Sustaining Healthy Family Habits | 1. Looking Back
2. Looking Forward
3. Continuing to Use Your Resources |
|------------------------------------------------------|------------------------------------------------------------------------------|

**7. Incentives for Participation:**

Participating parents will receive a \$15 gift card for each of the 2 surveys (baseline and 12-week follow-up), for a total of up to \$30. In addition, parents will also receive all ingredients necessary to prepare recipes as outlined in the attached Teaching Kitchen outreach program. All ingredients will be delivered to participants' homes by a credible and current home grocery delivery program used by Vanderbilt University Medical Center, such as Shipt or Instacart. Both the adapted Teaching Kitchen Outreach and adapted Healthier Families programming will be provided at no cost to the participating parent-child dyads.

**8. Randomization:**

Randomization will occur after obtaining informed consent as well as the completion of certain baseline data collected by the parent (i.e., the baseline survey). This process will be completed within a maximum of a 30-day period. Once successfully completed, randomization will occur. Within the first cohort of the trial, parent-child dyads will be grouped according to parent preferred language (English versus Spanish), resulting in two strata within each region. Dyads within the strata will be randomized to the intervention and control groups within each of the two regions for a total of up to 200 parent-child dyads. Participants will be randomized by an unblinded KSP. Participants will be told which group they were randomized to.

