## 4. Study Population and Sample Size:

In this randomized clinical trial, rolling recruitment will occur for approximately months starting in February of 2021 and running through May of 2021 until up to 200 participating parent-child dyads that fit the eligibility inclusion criteria as outlined below have been identified. Eligible participants whose providers have given permission will be contacted by key study personnel through email, text, or phone calls to invite them to participate in a study using a standard script. We will continue to contact eligible patients until we reach our recruitment goal. Participants will be recruited from the Vanderbilt Pediatric Primary Care Clinic or Nashville Collaborative community partner sites. This study will serve underserved populations, with limited access to financial resources. Low-income households, single-parent households, and households headed by Black or Latino adults - groups historically impacted by health disparities - experience a higher prevalence of food insecurity and reduced access to healthy foods, and they are thus appropriate targets for this study. These are also the populations that primarily comprise the populations served by Head Start, Parks and Recreation, Nashville Public Library, Project Transformation, Martha O'Bryan, and St. Luke's. Of those participants that meet eligibility and are enrolled in the study, all potential benefits and burdens are distributed fairly.

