**9. Statistical Analysis Plan:**

We will describe participant characteristics using mean (standard deviation [SD]) or frequency (percentage), as appropriate. Comparison of descriptive variables between the control group and intervention group will be performed using a chi-squared test for categorical variables and a 2-sample, independent t-test for continuous variables. We will test for changes between baseline and 12-week follow-up outcomes using paired t-tests for within group comparisons. We will test for changes between baseline and 12-week follow-up outcomes using 2-sample, independent t-tests for between-group comparisons of the intervention and control group. We will conduct Tobit regression models for scales in which there is a considerable degree of skewed data.

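### Randomisation uses language-by-region strata, but the between-group t-test ignores them, so the test may be conservative and lose some power

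*Protocol*

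**What the plan says.** Protocol section 8 (Randomization) sets the grouping rule: "Within the first cohort of the trial, parent-child dyads will be grouped according to parent preferred language (English versus Spanish"). It describes the outcome of this grouping as "resulting in two strata within each region". With two regions that makes 2 × 2 = 4 strata. The next sentence reads "Dyads within the strata will be randomized to the intervention and control groups within each of the two regions", and it attaches this to the whole trial: "within each of the two regions for a total of up to 200 parent-child dyads". Block size and allocation ratio are not stated. Neither the regions nor the cohorts are defined elsewhere in the protocol.

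Section 4 (Study Population and Sample Size) describes a single rolling recruitment, "until up to 200 participating parent-child dyads that fit the eligibility inclusion criteria". It gives no power calculation.

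Section 9 (Statistical Analysis Plan) tests changes from baseline to 12 weeks "using 2-sample, independent t-tests for between-group comparisons of the intervention and control group". I read this as a t-test on change scores. It adds: "We will conduct Tobit regression models for scales in which there is a considerable degree of skewed data". No covariates are named for either method.

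**The concern.** Stratifying on language and region treats them as factors worth balancing. When allocation is balanced within strata, differences between strata no longer contribute to the error of the treatment comparison. A pooled t-test still counts that variance in its standard error. The reported confidence interval is then wider than it need be and the p-value larger. The protocol gives no power calculation to show that precision can be spared, since 200 dyads is only a cap.

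Section 8 adds a smaller difficulty. It introduces the strata for the first cohort only, then randomises within strata up to the full total. Someone running the allocation could follow that text in two ways.

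**Working it through.** The protocol states no power, alpha, effect size or standard deviation for this comparison, so there is no figure of its own to reproduce. The following is conditional.

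**Inputs.** From the protocol: four strata and at most 200 dyads (section 8); a two-sample t-test on change with no stratum term (section 9). Assumed: two-sided alpha 0.05, 1:1 allocation, n = 100 per arm, no dropout, allocation balanced within strata for all dyads, and R2 (the strata's share of within-arm change-score variance) of 0 to 0.20. For power, an assumed true effect of 0.4 SD.

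**Step 1, standard errors in SD units.** The t-test estimates SE_est = √(2/n) = √(2/100) = 0.1414. Under balanced allocation the true value is SE_true = √(2(1 − R2)/n). The overstatement is 1/√(1 − R2) − 1. At R2 = 0.20 this is 1/√0.80 − 1 = 11.8%.

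**Step 2, type I error.** The true level is 2 × [1 − Φ(1.96/√(1 − R2))]. At R2 = 0.20: 1.96/0.8944 = 2.191, which gives 0.028.

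**Step 3, power at 0.4 SD.** Unadjusted: Φ((0.4 − 1.96 × SE_est)/SE_true). Adjusted for strata: Φ(0.4/SE_true − 1.96). At R2 = 0.20, SE_true = 0.1265, so unadjusted Φ(0.1228/0.1265) = Φ(0.971) = 0.834 and adjusted Φ(3.162 − 1.96) = Φ(1.202) = 0.885.

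| R2 | SE overstated by | True type I error | Power, unadjusted | Power, adjusted |
|---|---|---|---|---|
| 0 | 0% | 0.050 | 0.807 | 0.807 |
| 0.05 | 2.6% | 0.044 | 0.814 | 0.827 |
| 0.10 | 5.4% | 0.039 | 0.820 | 0.846 |
| 0.20 | 11.8% | 0.028 | 0.834 | 0.885 |

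**Step 4, simulation.** With 3,000 runs per setting, four strata, 200 dyads, blocks of 4 and an assumed 40% Spanish-speaking, the unadjusted test rejected a true null in 0.042, 0.029 and 0.031 of runs at R2 = 0.05, 0.10 and 0.20. The direction agrees with the table. The value at 0.10 lies below the formula's 0.039 by more than its simulation error, √(0.0388 × 0.9612/3000) = 0.0035, would usually explain, so I rely on the formula for size. Simulated power at R2 = 0.20 was 0.845 unadjusted and 0.895 adjusted.

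**Step 5, if allocation is not balanced within strata.** Under simple randomisation the t-test has about the right level (simulated 0.044 and 0.045 at R2 = 0.10 and 0.20), so steps 1 and 2 do not apply. Adjustment still helps: simulated power rose from 0.803 to 0.829 at R2 = 0.10 and from 0.798 to 0.870 at R2 = 0.20.

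**Step 6, the wording of section 8.** If the first cohort is the whole trial, the qualifier does no work. If later cohorts exist, they have no separate rule, yet the next sentence places all of the up to 200 dyads within strata. The two sentences cannot both be taken literally unless there is only one cohort.

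**The case against.** The strongest case against has four parts.

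- **R2 may be near zero.** Section 9 analyses change, and change scores already remove stable differences between language groups and regions. The relevant R2 is that of change, and the protocol gives no basis for any value. This stands, and it is why the range starts at nil.
- **The conservatism depends on balanced allocation.** Section 8 names no blocking. If only part of the sample were balanced, the effect would shrink: with half the dyads stratified and R2 = 0.10, the effective share is about 0.05 and the type I error about 4.4% rather than 3.9%. This also stands for steps 1 and 2. It does not remove the reason to adjust, as step 5 shows.
- **A separate analysis plan may add covariates.** Silence on the Tobit covariates is therefore not an error. The t-test, however, is stated outright in section 9.
- **The direction is safe.** An overstated standard error does not raise the false-positive rate. This stands.

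A reader might infer from the first-cohort wording that later cohorts are randomised without strata and that balance is lost there. The documents do not support that. No later cohort is defined, section 4 describes one rolling recruitment, and section 8 ties randomisation within strata to the full total. Nor can an analysis that omits the strata undo balance that the allocation has achieved.

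**Conclusion.** The mismatch holds: section 8 randomises within language-by-region strata, and section 9 fixes an unadjusted comparison. Its consequence is conditional and modest. With balanced allocation and an assumed R2 of 0 to 20%, the standard error is overstated by 0 to 11.8% and the true type I error runs from 5% down to 2.8%. In the illustration with 100 dyads per arm and an effect of 0.4 SD, the power lost is nil at R2 = 0, about 1 point at 0.05, about 3 at 0.10 and about 5 at 0.20. This is a loss of efficiency and no threat to validity.

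The first-cohort wording is a separate, minor ambiguity that needs reconciling. It is not evidence of imbalance between the arms.

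**What to change.** In section 9, replace the between-group t-test by a linear model of the 12-week score on arm, baseline score and the randomisation strata (language and region), and report the arm coefficient with its confidence interval. Put the same terms in the Tobit models.

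The cost is small. With 200 dyads the t-test has 198 residual degrees of freedom. A model with arm, baseline, language and region has 195, or 194 with a four-level stratum term. If the strata explain nothing, essentially nothing is lost.

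In section 8, define the two regions, and either define or remove the first-cohort qualifier, so that the text says stratification applies to all dyads. Section 4 planned recruitment through May 2021, and section 13 dates the final IRB revision to June 24, 2021. If allocation was already complete, the wording must record the rule that was actually used. The analysis change can be made either way.

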**9. Statistical Analysis Plan:**

We will describe participant characteristics using mean (standard deviation [SD]) or frequency (percentage), as appropriate. Comparison of descriptive variables between the control group and intervention group will be performed using a chi-squared test for categorical variables and a 2-sample, independent t-test for continuous variables. We will test for changes between baseline and 12-week follow-up outcomes using paired t-tests for within group comparisons. We will test for changes between baseline and 12-week follow-up outcomes using 2-sample, independent t-tests for between-group comparisons of the intervention and control group. We will conduct Tobit regression models for scales in which there is a considerable degree of skewed data.

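### Section 9 compares arms by unadjusted t-tests on change, giving up precision that ANCOVA on the collected baseline score, with language and region, would recover

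*Protocol*

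**What the plan says.** Section 9 of the protocol, which is itself headed as the statistical analysis plan, fixes four things that bear on this point.

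- Descriptors are tested for differences between arms: "Comparison of descriptive variables between the control group and intervention group will be performed using a chi-squared test" where they are categorical. Continuous descriptors get a two-sample t-test.
- Outcomes are compared within each arm "using paired t-tests for within group comparisons".
- Outcomes are compared between arms by "2-sample, independent t-tests for between-group comparisons of the intervention and control group". The sentence concerns the move from baseline to 12 weeks, so I read it as a t-test on change scores.
- For skewed scales: "We will conduct Tobit regression models for scales in which there is a considerable degree of skewed data".

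No covariate is named for any of these analyses.

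Section 8 groups dyads by parent preferred language, giving two strata in each region, and then: "Dyads within the strata will be randomized to the intervention and control groups within each of the two regions". The language grouping is stated for the first cohort. Section 8 also requires the baseline survey to be completed before randomisation, for a total of up to 200 dyads.

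**The concern.** Three features of the design do not fit together. The baseline survey is in hand before allocation, yet the baseline score enters the between-arm comparison only by subtraction. Language and region define the strata, yet neither appears in the analysis. The only baseline comparison at the analysis stage is a set of significance tests between arms formed by randomisation, where the null hypothesis is already true by design. A small p-value there is a chance finding, and a large one does not show that an imbalance is harmless.

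Precision and interpretability are at stake. Subtracting the baseline in full assumes in effect that a baseline difference carries through one-for-one to 12 weeks. With rho below 1 it does not, so the arm that starts higher by chance is penalised. The change score also carries more error variance than an adjusted comparison of the same data. In a trial of at most 200 dyads that loss is worth avoiding, since the covariates cost nothing to obtain.

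**Working it through.** **Inputs.** The protocol gives the total (up to 200 dyads, Section 8) and the tests (Section 9). It gives no allocation ratio, SD, correlation, effect size, alpha or power, so there is no figure of its own to reproduce. I assume n = 100 per arm, two-sided 0.05, 80% power and equal SDs at baseline and 12 weeks. Rho is varied from 0.3 to 0.8. Differences are in SD units of the score.

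**Step 1: shift from a chance imbalance.** If the arms differ by d SD at baseline, the change contrast is shifted by (rho − 1) × d. With d = 0.20:
- rho 0.5: (0.5 − 1) × 0.20 = −0.10 SD
- rho 0.7: (0.7 − 1) × 0.20 = −0.06 SD

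Under a linear model ANCOVA removes this shift.

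**Step 2: how often.** An imbalance of 0.20 SD gives a test statistic of 0.20 / sqrt(2/100) = 1.41 and p = 0.16. One at least this large, in either direction, therefore arises in about 16% of such trials for any given score.

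**Step 3: error rate given the imbalance.** The contrast then has mean (rho − 1)d and true SD sqrt((1 − rho²) × 2/n), while the t-test uses the standard error sqrt(4(1 − rho)/n). For d = 0.20 the conditional type I error is 7.5% at rho 0.5 and 6.6% at rho 0.7. For d = 0.10 it is 3.6% and 4.1%. It lies below 5% for small imbalances and above 5% for larger ones, and the overall rate remains 5%.

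**Step 4: precision.** The detectable difference is (1.96 + 0.84) × sqrt(2v/n), with v = 2(1 − rho) for the change score and v = 1 − rho² for ANCOVA. The variance ratio is (1 − rho²) / (2(1 − rho)) = (1 + rho)/2.

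| rho | Change score, SD | ANCOVA, SD | Variance ratio |
|---|---|---|---|
| 0.3 | 0.469 | 0.378 | 0.65 |
| 0.5 | 0.396 | 0.343 | 0.75 |
| 0.7 | 0.307 | 0.283 | 0.85 |
| 0.8 | 0.251 | 0.238 | 0.90 |

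Put another way, 200 dyads analysed by ANCOVA carry the information of 200/0.75 = 267 dyads analysed by change score at rho 0.5, or 200/0.85 = 235 at rho 0.7. Any further gain from language and region is not counted.

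**Step 5: do the descriptor tests help?** At 100 per arm a t-test reaches p < 0.05 only at an imbalance of about 0.28 SD (1.972 × sqrt(2/100) = 0.279). Even if baseline outcome scores were among the variables tested, which Section 9 does not say, the 0.20 SD imbalance of Step 1 would go unremarked. Conversely, taking race/ethnicity, age and sex of parent and child as six descriptors (Table 1) and treating the tests as independent, the chance of at least one p < 0.05 is 1 − 0.95⁶ = 26%. The tests are plainly correlated, so this is only a rough guide.

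**The case against.** The strongest defence is that the planned comparison is legitimate. Under randomisation a t-test on change is unbiased and holds its 5% error rate over repeated allocations, and its standard error already allows for chance imbalance. That stands. The case for changing it rests on lost precision and on the shift conditional on the imbalance that actually occurs.

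A reader might infer several stronger things that the protocol does not support.

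- *That the descriptor tests are the plan's only means of handling baseline differences.* Stratification in Section 8 controls language and region by design, at least in the first cohort.
- *That the outcome tests take no account of baseline.* The change score subtracts it. The fault is that it subtracts too much when rho is below 1.
- *That the descriptor p-values decide adjustment or certify balance.* Section 9 gives them no such role. Nor does it say that language, region or the baseline outcome scores are among the variables tested. Deleting the p-values would by itself change no estimate.

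It can also be said that a separate analysis plan might add covariates. It might, but Section 9 states a specific test rather than deferring the choice, so the two would then have to be reconciled.

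**Conclusion.** The point holds as a matter of efficiency and of robustness to chance imbalance. It does not show that the planned test is invalid. Given 100 dyads per arm and equal SDs, the plan forgoes a reduction in error variance to 0.75 of its value at rho 0.5, or 0.85 at rho 0.7. It also leaves exposure to a shift that, for a 0.20 SD imbalance, is about a quarter of the detectable difference at rho 0.5 (0.10 against 0.40 SD) and about a fifth at rho 0.7 (0.06 against 0.31 SD). The gain shrinks as rho approaches 1. Allocation ratio, SDs and rho are all assumptions. With fewer dyads analysed, detectable differences grow under both methods, but the variance ratio depends only on rho. The baseline p-values are a minor accompanying matter: uninformative, but without a stated effect on any result.

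**What to change.** In Section 9, replace the sentence specifying between-group t-tests; adding covariates alongside it would leave a contradiction, because a two-sample t-test takes none. Suggested wording: *The 12-week score of each outcome will be compared between arms by a linear model (ANCOVA) with terms for arm, the baseline value of that outcome, parent preferred language and region. These covariates will be included whatever the observed balance. Where a Tobit model is used, it will include the same covariates.*

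Because the language grouping is stated for the first cohort, the text should also confirm that preferred language is recorded for dyads in any later cohort.

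As a minor accompanying change, replace the sentence on comparing descriptive variables with a statement that they will be reported by arm as mean (SD) or n (%), without p-values.

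The cost is a few sentences in Section 9. No new data collection is planned or needed: the baseline survey precedes randomisation, and language and region are already used to form the strata.

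### The between-arm t-test on change leaves out the baseline score: valid with complete data, but less efficient than ANCOVA, and biased if the relation of dropout to baseline differs between arms

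*Protocol*

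**What the plan says.** Section 9 gives the randomised comparison in one sentence: change from baseline to 12 weeks is tested "using 2-sample, independent t-tests for between-group comparisons of the intervention and control group". It names no covariate. Within each arm the same change is tested "using paired t-tests for within group comparisons". For some scales a regression model is foreseen: "We will conduct Tobit regression models for scales in which there is a considerable degree of skewed data". Section 9 does not say which covariates those models contain.

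Section 8 sets the order of events: "Randomization will occur after obtaining informed consent as well as the completion of certain baseline data", with the baseline survey named as the data meant. Section 7 confirms two assessments, with a gift card "for each of the 2 surveys (baseline and 12-week follow-up"). The size is given only as a maximum, "for a total of up to 200 parent-child dyads" (Section 8). Section 8 also says that participants learn their group. Under Section 6, only the intervention arm receives the weekly health coaching.

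**The concern.** The between-arm comparison is the one that tests the last sentence of the hypothesis in Section 3, that the intervention group improves more than control. A difference of change scores fixes the coefficient of baseline at 1. With equal SDs the coefficient that minimises the variance is rho, which is below 1, so part of the baseline variation is added to the contrast instead of removed. The baseline score is already collected, so using it requires no new data.

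A second issue follows from the same choice. The t-test can use only dyads with both surveys, and it does not condition on baseline. If the families who leave the coaching arm have a different baseline profile from those who leave the control arm, the completers differ at baseline. Regression to the mean then appears as a difference in change.

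At stake are the power of the main contrast, with the number of dyads capped, and its protection against one form of selective loss.

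**Working it through.** **Inputs from the protocol.** Change-score t-test without covariates (Section 9); baseline survey before randomisation (Section 8); at most 200 dyads (Sections 4 and 8). The protocol gives no alpha, power, SD, effect size, rho, dropout rate or allocation ratio, so it has no figure of its own to reproduce.

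**Assumptions.** Two-sided 5%, 1:1 allocation, hence n = 100 per arm with no dropout; equal SDs at both times; rho from 0.3 to 0.9.

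**Step 1, variance.** Per dyad, in units of SD²:

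- change score: 2(1 − rho)
- ANCOVA: 1 − rho² = (1 − rho)(1 + rho)
- ratio ANCOVA/change: (1 + rho)/2

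The direction does not depend on equal SDs. In general Var(change) = Var(ANCOVA) + (SD at baseline − rho × SD at 12 weeks)², so in large samples the change score is never the more precise of the two.

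**Step 2, detectable difference and power.** The standard error is the square root of the per-dyad variance times √(2/n), with √(2/100) = 0.1414. The difference detectable with 80% power is 2.80 × SE. At rho = 0.5:

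- change score: 2.80 × √1.00 × 0.1414 = 0.396 SD
- ANCOVA: 2.80 × √0.75 × 0.1414 = 0.343 SD

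| rho | variance ratio | detectable difference, change | detectable difference, ANCOVA | power at 0.40 SD, change | power at 0.40 SD, ANCOVA |
|---|---|---|---|---|---|
| 0.3 | 0.65 | 0.469 | 0.378 | 66.7% | 84.3% |
| 0.5 | 0.75 | 0.396 | 0.343 | 80.7% | 90.4% |
| 0.7 | 0.85 | 0.307 | 0.283 | 95.5% | 97.7% |
| 0.9 | 0.95 | 0.177 | 0.173 | about 100% | about 100% |

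With 80 per arm (20% dropout assumed), power at 0.40 SD goes from 57.1% to 75.6% (rho 0.3), 71.6% to 83.2% (0.5) and 90.4% to 94.3% (0.7).

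**Step 3, bias from dropout.** With no treatment effect and scores in SD units, expected change given baseline x is −(1 − rho)x. The expected difference in change among completers is therefore −(1 − rho) times their baseline difference between arms. It is zero if completers have the same mean baseline in both arms.

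A simulation under no effect (4,000 trials, 100 per arm, dropout logistic in baseline, about 25% to 29% lost overall) agrees:

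| dropout log-odds slope per SD of baseline (control; intervention) | bias of change-score test (SD), rho 0.3 / 0.5 / 0.7 | type I error, rho 0.3 / 0.5 / 0.7 |
|---|---|---|
| 1; 1 (same in both arms) | 0.003 / 0.002 / 0.003 | 4.3% / 4.6% / 5.3% |
| 0; 1 | 0.169 / 0.116 / 0.070 | 13.8% / 11.6% / 8.6% |
| −1; 1 | 0.332 / 0.238 / 0.148 | 39.5% / 30.4% / 21.1% |

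The second row fits the formula: 0.169/0.7, 0.116/0.5 and 0.070/0.3 all imply a completer baseline gap of about 0.23 to 0.24 SD. The sign reverses if low scorers are the ones lost from the coaching arm. ANCOVA stayed within 0.005 SD of zero in all these cases, with type I error of 4.6% to 5.6%. The dropout patterns are hypothetical and show the mechanism only.

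**The case against.** In a randomised trial with complete data, a t-test on change is valid and unbiased, and no figure in the protocol is contradicted. That stands. The gain rests on a correlation the protocol does not give; for scales repeated after only 12 weeks it could be high, and at rho 0.9 there is little to win. That also stands. However, some outcomes are very short (one general-health item and three parent sleep items in Table 1), so a high rho cannot be presumed for all of them.

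A reader might infer that the test is biased whenever dropout depends on baseline. The documents and the arithmetic do not support this: when the dependence is the same in both arms, the bias is nil. The relation must differ between arms. Unequal coaching burden and knowledge of the assigned arm make that possible. On the other side, both arms receive groceries and videos (Section 6) and the same survey incentive (Section 7), and surveys may be done by phone, on paper or online (Section 10). Differential loss is neither documented nor ruled out.

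A reader might also infer that ANCOVA removes dropout bias in general. It does so here because dropout was simulated to depend only on arm and baseline. Where the effect itself varied with baseline and dropout was equally baseline-related in both arms, both methods gave 0.228 against a true 0.300.

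Two practical limits stand as well. ANCOVA on the 12-week score still omits dyads without a 12-week survey. And Section 10 anticipates incomplete survey data, so an occasional scale may lack a baseline score even though the survey precedes randomisation.

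The last objection is timing. Recruitment was planned to end in May 2021 (Section 4), while the document records trial registration in April 2022 (Section 13). If recruitment kept to plan, 12-week data were in hand by then, and a silent replacement of the test would be post hoc. The documents do not say whether anyone had seen outcome data.

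**Conclusion.** The point holds as one of efficiency, with a conditional risk of bias. The planned test is not invalid. Its contrast has a larger variance than ANCOVA for any rho below 1 under equal SDs: ANCOVA needs 65%, 75%, 85% or 95% of the dyads for rho of 0.3, 0.5, 0.7 or 0.9. At rho 0.5 and 100 per arm, the detectable difference drops from 0.40 to 0.34 SD, and power at 0.40 SD rises from 81% to 90%. These figures assume 1:1 allocation, a two-sided 5% level and no dropout.

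Bias arises only if the relation of dropout to baseline differs between arms. Its size here is unknown, because the protocol gives no dropout rates.

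The criticism of the missing covariate applies to the t-test. For the Tobit models the covariates are simply unstated. A separate analysis plan may exist, but the protocol itself fixes the t-test in Section 9.

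**What to change.** Replace the between-group sentence in Section 9 with wording such as: *The 12-week score will be compared between arms, as randomised, by a linear model with the baseline score of the same scale as covariate, in all dyads with a 12-week score; the estimated difference and its 95% confidence interval will be reported. Tobit models for skewed scales will include the same baseline covariate. The t-test on change will be reported as a sensitivity analysis.*

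A constrained longitudinal mixed model is an option if dyads with only a baseline survey are to be retained. It is a different analysis set, so the plan should say which model is used.

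The cost is a few sentences and no new data. If outcome data have already been seen, report the planned t-test as planned and label the adjusted analysis as added afterwards.
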